
### Formulation of anxiety and treatment planning

Once the assessment is complete, the RA will compile a standardised assessment report including the following information:
Current (and, where relevant, historical) mental health and physical health diagnosis(es) including severity scores from the ADIS-5 diagnostic interviewRelevant personal details/background, the impact autism and anxiety may have on the current functioning and a summary paragraph of each anxiety/mental health disorderSRS-2 and TAS-20 summary scoresA summary of reasonable adjustments required for therapyTwo target-situation vignettesThe Session Engagement Form

The assessment report for each consented participant will be discussed at a meeting of trial therapists and senior members of the research and clinical team convened by the RA. During this meeting, a formulation of the participant’s current anxiety-related difficulties will be developed and an individualised treatment plan agreed prior to randomisation. Decisions regarding treatment planning will be informed by a treatment algorithm developed by the clinical team as part of the trial. The treatment algorithm uses the assessment information and the participant’s target situations to plan treatment using a combination of the treatment modules available. Following the answering of any questions on the presentation, the RA will leave the room, and the clinical team will agree a treatment plan. In addition, as part of the evaluation of the feasibility of the formulation and treatment planning procedures, prior to the meeting, the RA will use the treatment algorithm to identify the treatment plan that they suggest, and seal this in an envelope to be opened at the end of the formulation meeting. Levels of agreement in treatment plans between the RA and the clinical team will be calculated; however, for the purpose of this pilot RCT the clinical team’s decision will be final.

### Feasibility and acceptability outcomes

The primary outcomes for this feasibility and acceptability pilot RCT will be recruitment (number of expressions of interest, how many of those expressing interest go on to consent (and, if not, why not?), how many are excluded and the reasons for this), acceptability (including acceptability of the randomisation procedure), retention, completion of outcome measures and treatment adherence. Treatment adherence will be measured by recording the percentage of sessions that each participant attended, compared with those scheduled and reporting the median, minimum and maximum for the sample. As treatment is individualised and, therefore, variable in length, there is no fixed number of sessions for a ‘complete’ dose. The therapist will also record each participant’s engagement in homework tasks (a core component of CBT) at each session. The participant’s engagement will be rated on a 5-point scale ranging from ‘not attempted’ to ‘extra homework completed’. Each participant’s engagement in homework will be combined into an average score over the course of their treatment and the median, minimum and maximum at sample level will be reported.

An opportunity to participate in a semi-structured qualitative interview will be offered to all participants 3 months post intervention, with the aim of gaining information about the acceptability of the trial and treatment processes from the participant’s perspective. Topics to be covered will include the acceptability of randomisation, feedback on both the PAT-A© intervention and CCSP and the appropriateness of baseline and outcome measures used. Participants will also be asked if they have experienced any changes (either positive or negative) in any other anxiety-related situation not otherwise covered in the target situation(s).

### Other outcomes

As the PAT-A© intervention has been developed to improve engagement with the specific target situations, the target situation rating will also be considered as an outcome measure to identify symptom change over time. As previously described two target situation vignettes will be developed in collaboration with the participant using baseline assessment data. Both vignettes and the severity of difficulties within the target situation are then reassessed 3 months post intervention by the RA. Degree of improvement will be rated by an expert panel of researchers and clinicians, blinded to the treatment group, which will compare the anonymised vignettes from baseline and follow-up and identify whether there has been any change since baseline. A 9-point scale (from 1 ‘normalised’, 2 ‘markedly improved’, 3 ‘definitely improved’, 4 ‘equivocally improved’, 5 ‘no change’, 6 ‘equivocally worse’, 7 ‘definitely worse’, 8 ‘markedly worse’ to 9 ‘disastrously worse’) will be used to rate change between baseline and 3 months post intervention. Comparisons of change scores for the two vignettes between the two groups across time (baseline to 3- month follow-up) will then be made. The research team also plans to repeat the target-situation interview and ratings at 12 months post intervention.

In addition to the target situations, the following questionnaire data will be collected at 3 months post intervention to allow analysis of differences between baseline and follow-up across the intervention and control groups:
• Anxiety: assessed using the full-scale score on the ASA-A• Quality of life: assessed using full-scale score and subscale scores on the WHOQoL-BREF plus the ASQoL and disabilities module• Health-related quality of life: assessed using full-scale score on the EQ-5D

The Clinical Global Impression of Improvement (CGI-I) will be used to assess global clinical change between baseline and 3 months post intervention. The CGI-I is a standardised framework for clinicians to assess to what extent participants’ symptoms have improved or worsened using a 7-point scale (1 – very much improved; 2 – much improved; 3 – minimally improved; 4 – no change; 5 – minimally worse; 6 – much worse; or 7 – very much worse). The RA, who is blind to group and clinically trained, will rate global improvement using all available data from baseline and 3-month post-intervention follow-up, including:
ASA-AWHOQoL-BREF plus ASQoL and disabilities moduleEQ-5DHADS-D (depression subscale)Target-situation vignettesResponses to the interview question about change in an anxiety-related situation not otherwise included in the target-situation vignette(s)

Ratings of 1 (very much improved) and 2 (much improved) are regarded as significant ‘improvement’, ratings of 7 (very much worse) and 6 (much worse) are regarded as significant ‘worsening’ and ratings of 3–5 (inclusive) are regarded as ‘no change’. A percentage of the participants’ CGI-I score will be independently rated by a second rater to assess inter-rater reliability.

Full details of the measures repeated at follow-up can be seen in Fig. 2.

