Social Responsiveness Scale (SRS-2; [53]: the SRS-2 is a standardised self-report questionnaire used extensively to rate the social communication difficulties of autistic adults and children. Estimates of internal consistency of between .94 to .96 have been reported whilst the predictive validity of the adult form found a specificity level of .60 and sensitivity of .86 [54]Anxiety Scale for Autism–Adult (ASA-A©; [55]): the ASA-A© is a 20-item self-report measure designed to measure anxiety in autistic adults. It consists of four subscales: Social Phobia (SP), Anxious Arousal (AA) and Uncertainty (U). The ASA-A© can be summated to provide a total anxiety score, as well as broken down into subscale scores (the sum of items within a subscale). All items are rated on a 4-point Likert scale, from 0 (‘never’) to 3 (‘always’). The ASA-A© was adapted from the Anxiety Scale for Children Autism Spectrum Disorder (ASC-ASD©; [56]) in collaboration with professionals and autistic adults, to make it suitable for use in an adult population. The authors indicate that a total score of ≥ 28 on the ASA-A© may indicate the presence of significant levels of anxiety. At present, indicative cut-offs are not available for the subscales. Preliminary analysis of the psychometric properties of the ASA-A© indicate excellent internal consistency (Cronbach’s α total score = .899, Uncertainty subscale = .834, Anxious Arousal Subscale = .845, Social Phobia Subscale = .847), excellent 1-month test-retest reliability (.823) and robust convergent and divergent validity [55]Hospital Anxiety and Depression Scale (HADS; (Zigmond AS, Snaith RP. The Hospital Anxiety and Depression Scale, submitted)): the HADS is a 14-item self-report questionnaire widely used within a variety of community and psychiatric populations in order to measure symptoms of anxiety (seven items) and depression (seven items). Research demonstrates promising internal consistency (HADS-A, *α* = 82–.84; HADS-D, .60–.72) and convergent validity (WEMWBS, *r* = −.45 to −.60, *p* < .001; SDQ emotional scale, *r* = .80, *p* < .001; *DSM-5* DAS anxiety scale, *r* = .71, *p* < .001 and the PHQ-9 depression scale, *r* = .56, *p* < .001) when used with autistic individuals [57]WHO Quality of Life-BREF (WHOQOL-BREF) and Disabilities module plus Autism Addendum: the WHOQOL-BREF [58] is an abbreviated 26-item questionnaire covering four domains of quality of life (Physical health, Psychological health, Social relationships, and Environment). It is currently the most commonly used quality of life measure within autistic adult populations [59]. In order to ensure relevance to our participant group the WHOQOL-BREF will be used alongside the WHO Disabilities module [60] and the Autism Addendum recently developed by our group [61]. Internal consistency for this measure is excellent (*α* = 0.93) whilst the structural validity of the WHO factor structure is acceptable for use with autistic people (CFI = 0.902, GFI = 0.886, RMSEA = 0.059, PCLOSE = 0.006, *χ*^2^ = 519.90, *df* = 242, *p* < 0.001) [61]EuroQoL 5 dimensions, 5 levels health survey (EQ-5D): the EQ-5D [62] is a generic measure of health-related quality of life allowing for the calculation of Quality Adjusted Life Years (QALYs), commonly used by the NHS to measure treatment effectiveness. There is evidence that the measure demonstrates convergent validity with all items of the World Health Organisation-Five Well-Being Index (WHO-5; [63])Toronto Alexithymia Scale-20 (TAS-20; [64]: the TAS-20 is one of the most commonly used measures of alexithymia comprising of three subscales covering difficulty describing feelings, difficulty identifying feelings, and externally-orientated thinking. It has demonstrated test-retest reliability (*r* = 0.79–0.92), convergent validity with other measures of alexithymia such as the Bermond and Vorst Alexithymia Questionnaire-form B (BVAQ-B; *r* = 0.48–0.77, *p* < 0.05) and discriminant validity, over time, in a sample of autistic adults and controls (time 1, Exp(B) = 1.22, CI (1.09–1.36), *p* < 0.001; time 2, Exp(B) = 1.17, CI (1.06–1.29), *p* < 0.01) [65]Waisman Activities of Daily Living Scale (W-ADL; [44]: the Waisman Activities of Daily Living Scale (W-ADL) is a measure of independence validated in people with a broad range of developmental disability diagnoses. Analysis indicates that it is reliable over time (*κ* = 0.92–0.93), with high levels of internal consistency across disability groups (Cronbach’s *α* = 0.88–0.94) and criterion validity when compared to the Vineland Screener Adaptive Behavior Composite Score (*r* = 0.78)Reasonable adjustments: an adaptation of an existing checklist, will be utilised. As autistic adults state that they would like professionals to take into account their sensory sensitivities or neurological differences [12, 13], we will aim to accommodate these within the intervention by asking participants as part of the baseline characterisation about their preferred means of communication, factors which may make attending sessions easier/more difficult, current emotional-regulation techniques, special interests and considerations regarding the involvement of family members, friends or independent advocates

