### Statistical analysis

As this is a feasibility and acceptability pilot study, analyses will be mainly descriptive. Formal power calculations are not appropriate as the study is not designed to test for a difference between treatments. Feasibility will, therefore, be explored by examining:
The number of expression-of-interest forms received, the number who go on to consent and those who either choose not to take part (including reasons given) and those who are ruled out on eligibility groundsTake-up, attendance and engagement with the PAT-A© intervention and CCSPCompletion of follow-up data at 3 months and 12 months post interventionQualitative data regarding the acceptability of PAT-A© from the participants’ perspective

We will also undertake some preliminary analysis of treatment effects, and follow a pre-existing statistical analysis plan. The difference in mean change as assessed by the main outcome measure from our previous trials (‘target-situation’ vignettes) and anxiety screening tools will be examined between the groups from baseline to 3 months post intervention with accompanying 95% confidence intervals. Results will be interpreted cautiously because of the size of the study, the possible imbalance in pre-randomisation baseline covariates and the range of interventions offered to participants within the CCSP arm of the trial (Fig. 3).

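### The article is inconsistent on whether the HADS is collected at 3 months and on which anxiety questionnaires are compared between arms; a minor point, fixed by listing the full HADS and naming the tools

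*Protocol article*

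**What the plan says.** Four places in the protocol article bear on this.

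- **Baseline characterisation.** The HADS is in the baseline self-report set. It is described as one 14-item form, with seven anxiety and seven depression items.
- **Other outcomes, questionnaire list.** The article states that "the following questionnaire data will be collected at 3 months post intervention to allow analysis of differences between baseline and follow-up" across the two groups. Three entries follow: "Anxiety: assessed using the full-scale score on the ASA-A"; the WHOQoL-BREF with the autism and disabilities modules; and "Health-related quality of life: assessed using full-scale score on the EQ-5D". The HADS does not appear.
- **Other outcomes, CGI-I.** The blinded research associate "will rate global improvement using all available data from baseline and 3-month post-intervention follow-up, including" six named inputs, one of which is the HADS depression subscale. The section closes with "Full details of the measures repeated at follow-up can be seen in Fig. 2". That figure is not reproduced in the text at hand.
- **Statistical analysis.** The difference in mean change on the target-situation vignettes and on "anxiety screening tools will be examined between the groups from baseline to 3 months post intervention with accompanying 95% confidence intervals". The tools are not named.

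**The concern.** The questionnaire list is worded as a statement of what is collected at 3 months. Read that way, it leaves out a form that the CGI-I paragraph needs at the same visit. The analysis section speaks of more than one anxiety tool, but the list supplies one. The only other self-report questionnaire in the baseline set described as measuring anxiety symptoms is the HADS, so a reader cannot tell whether HADS-A is an outcome.

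Three things are at stake, all modest:

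- which forms participants are given at follow-up;
- which forms count towards completion of outcome measures, one of the primary feasibility outcomes;
- which anxiety comparisons are reported with confidence intervals.

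The Trial status section reports that recruitment was still open at submission. Answers not collected at 3 months could not be recovered later.

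**Working it through.** **1. Setting the lists side by side.** The plan gives no figure to reproduce here; the check is a count.

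| Questionnaire | Baseline set | 3-month list | CGI-I input (baseline and 3 months) |
|---|---|---|---|
| ASA-A | yes | yes | yes |
| WHOQoL-BREF with modules | yes | yes | yes |
| EQ-5D | yes | yes | yes |
| HADS | yes, all 14 items | no | depression subscale only |

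The CGI-I uses four questionnaires and the 3-month list holds three. The HADS is the single mismatch. The list contains one anxiety questionnaire, while the analysis wording is plural.

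**2. What the unseen schedule figure could settle.** If it shows the HADS at 3 months, the questionnaire list is incomplete as a statement of what is collected. If it does not, it disagrees with the CGI-I inputs. A text correction is needed in either case, but only the second case would mean a missing input.

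**3. Precision of an anxiety comparison.** These figures apply to any continuous questionnaire score, so they do not measure the inconsistency. They show what naming the tools and adjusting for baseline would give.

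Inputs: up to 40 participants (Sample size section), taken as 20 per arm with no attrition. The baseline/follow-up correlation r is an assumption, 0.6 with a range of 0.5 to 0.7; the article gives none. Results are in units of the between-person SD, assumed equal at both times.

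- Follow-up scores alone: t(0.975, 38) × √(2/20) = 2.024 × 0.316 = 0.64 SD.
- Difference in mean change: t(0.975, 38) × √[(2/20) × 2(1 − r)]. For r = 0.6: 2.024 × √0.080 = 0.57 SD.
- Baseline-adjusted (ANCOVA): t(0.975, 37) × √[(2/20)(1 − r²)]. For r = 0.6: 2.026 × √0.064 = 0.51 SD.

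| r | Follow-up only | Change score | Baseline-adjusted |
|---|---|---|---|
| 0.5 | 0.64 | 0.64 | 0.55 |
| 0.6 | 0.64 | 0.57 | 0.51 |
| 0.7 | 0.64 | 0.50 | 0.46 |

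At r = 0.6 adjustment narrows the change-score interval by about 10% (0.513/0.573 = 0.895). The ANCOVA formula ignores the small loss from chance baseline imbalance. The article allocates by simple randomisation, so an exact 20/20 split is also an idealisation. Attrition or an uneven split would widen all three intervals.

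**The case against.** The strongest reply is that the passages can be read together. The list's stated purpose is analysis of differences across the two groups, and it does not say that nothing else is collected. The next paragraph makes HADS-D part of the 3-month data for the CGI-I. On this reading HADS-D is collected as a CGI-I input and is simply not a between-group outcome. The section then sends the reader to the figure for the full schedule, and the plural may be loose wording that the separate statistical analysis plan resolves.

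Much of this stands. It defeats two stronger inferences that a reader might draw:

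- **That the CGI-I will lack its follow-up HADS-D.** The CGI-I paragraph implies that the subscale is collected, and the figure that would confirm or refute this cannot be seen.
- **That between-arm anxiety change rests on one questionnaire.** The target-situation vignettes concern anxiety-provoking situations, are rated by a blinded panel and are also compared between arms.

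Nor is the ASA-A a weak choice. It was designed for autistic adults, and the article gives its total score an internal consistency of .899.

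The reply does not remove the inconsistency. The list's verb is about collection, and the co-operative reading still leaves the plural anxiety tools unexplained. Which forms participants complete is a matter this article itself sets out, so it should do so consistently.

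**Conclusion.** The point holds as a minor inconsistency. The 3-month list omits the HADS, the CGI-I uses HADS-D at 3 months, and the analysis compares unnamed anxiety tools in the plural while one is listed. This rests on the text alone. Loss of data is not shown. The sample size is unaffected, and the primary feasibility outcomes are touched only through which forms count as completed.

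Two improvements are worth making while the wording is corrected. HADS-A at 3 months is cheap, because the form is already needed for HADS-D. It is free only if the full form would be given anyway, which the text does not say. Baseline adjustment uses data already collected and, under the stated assumptions, shortens the half-width from about 0.57 to 0.51 SD (0.64 to 0.55 at r = 0.5; 0.50 to 0.46 at r = 0.7).

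**What to change.** - **Other outcomes:** add the full 14-item HADS to the questionnaires collected at 3 months, and make the schedule figure (Fig. 2) agree.
- **Statistical analysis:** name the ASA-A total as the main anxiety questionnaire and HADS-A as a supporting one. Report each as a baseline-adjusted (ANCOVA) difference between arms with a 95% confidence interval, in place of the difference in mean change. The panel's vignette rating is already a rating of change from baseline, so this applies to the questionnaires only.
- **CGI-I:** no change is needed. Its inputs are already open to whatever data are available, so HADS-A is admitted once collected.

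Cost: wording in two sections and the figure, at most seven extra items per participant at one visit, and one more descriptive comparison to report.

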**Fig. 2 Fig2:**
[figure not shown]
Standard Protocol Items: Recommendations for Interventional Trials (SPIRIT) Figure: schedule of enrolment, intervention and assessment within the Personalised Anxiety Treatment–Autism (PAT-A©) trial

### Data collection and management

Baseline assessment and follow-up measures will be collected by a RA blinded to the outcome of randomisation. All participants will be allocated a unique number that will be used to identify them on all paper assessment forms throughout the trial. All data collected on paper will be inputted into a statistical analysis software system and all identifying data will be stored separately. A proportion of the data recorded on paper will be inputted electronically by two researchers independently to measure data-entry error rate. Missing questionnaire data at item level will be managed according to the manual for each questionnaire. If no manual exists, any published precedents will be consulted (e.g. [66]), or the mean imputed score for that subscale/full-scale (as appropriate) will be used, providing that no more than 30% of the data is missing. All study data will be treated in accordance with the latest Directive on Good Clinical Practice (2005/28/EC).

A Data Monitoring Committee (DMC) will not be required as this is a pilot feasibility trial. The RA will discuss challenges with data collection with the lead investigators. The RA will be responsible for ongoing review of data completeness and any concerns will be discussed within the wider research team and the sponsor as appropriate.

### Treatment fidelity and engagement

The PAT-A© intervention has been designed to be delivered by clinical psychologists or suitably qualified CBT therapists with experience of working with autistic adults. Therapists will receive supervision every 2 weeks, alongside monthly group supervision and access (as and when required) to a consultation group of researchers and clinicians (comprising experts in CBT and adapting interventions for autistic people). A Session Recording Form will be completed by the therapist after each therapy session in order to track the treatment modules and specific components received by the participant and to assess therapist adherence to core CBT techniques (e.g. guided discovery, ‘homework’ setting). Where possible, therapy sessions will be audio-recorded in order to undertake independent fidelity ratings after all participants have been treated. Members of the research team will review audio-recorded sessions to ensure fidelity to the treatment module(s) as they are defined in the manual(s).

The session engagement checklist used during assessment (described above) will also be used after each therapy session to assess and record the participant’s engagement with treatment and to facilitate therapeutic review including impact of any required autism informed adjustments to therapy, or additional adjustments required.

